## Background

In recent years, the improvement in cancer treatments and broad support for preventive strategies have enabled us to reach a higher rate of early diagnosis and a better understanding of the oncologic pathology itself, thus achieving an exponential increase in the five-year survival of patients with cancer [1].

Linked to that increase in survival, and due to the resulting increase in the lines of treatment employed, we are seeing greater side effects, which have repercussions in aspects such as the patients’ functionality and their quality of life [2]. Some of these side effects include cancer-related asthenia, anxiety, and dyspnoea [3]. Dyspnoea may represent a serious health problem, with considerable limitations for the individuals. In some patients with advanced-stage cancer, this dyspnoea may represent a clinical sign of the final phase of the disease [4]. Approximately 41% of the patients in palliative care have dyspnoea, and 46% of those describe it as being moderate or severe [5, 6].

The majority of patients perceive this dyspnoea to be a limiting factor that is out of their control, which leads them to adopt behaviours which have negative repercussions on their functionality [7], such as cancer patients creating patterns of fear/avoidance of movement or of physical activity, as is often the case also with patients with chronic pain, chronic fatigue syndrome, or fibromyalgia [8, 9]. It is similar to when patients with respiratory problems decrease their level of activity to adapt to their symptomatology. This favours a worsening of their physical state and of the dyspnoea upon exertion, known as the “cycle of the respiratory patient” [10].

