### Sample/participants

#### Participants

The patients will be recruited from the Oncology Hospitalisation Unit at the CAUSA, and must meet the following selection criteria: A) Inclusion criteria: Participants must have a pathological diagnosis of an oncological disease, be over 18 years of age, be hospitalised at the time of recruitment in the Oncology Unit at CAUSA, meet dyspnoea parameters of 2 or more points on the Medical Research Council scale (MRC), receive fewer than 85 points on the Barthel Index, and have signed an informed consent form indicating voluntary agreement to participate in the study. B) Exclusion criteria: not having an adequate cognitive state to be able to comprehend and follow the orders provided (fewer than 23 points on the Mini Mental State Examination, MMSE), having a haemoglobin level lower than 10 g/dL, being an active smoker at the time of recruitment. C) Withdrawal criteria: disease progression which brings the patient to a terminal situation or to death, and non-completion of the follow-up and final assessments.

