#### Sample size

The sample size has been estimated based on the potential modification of the most stringent of the principal variables of the study—the score on the Barthel Index. For this, as a reference, we have used the results obtained in a study with similar characteristics, in which the scoring on the Barthel Index was modified by 7.5 points [17]. With these premises, accepting an alpha risk of 0.05 and a beta risk of 0.2 in a bilateral contrast, we will need 25 subjects in the first group and 25 subjects in the second group in order to detect a difference greater than or equal to 7.5 units. The assumed common standard deviation is 8.3. We estimate a rate of 20% lost to follow-up. The sample size was estimated using the programme EPIDAT 4.2.

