### Procedures and data collection

#### Evaluations and study plan

Three assessments will be completed in this study: one at the beginning, another after 7 days, and a final one before the patient is discharged from hospital. After recruitment and before randomisation and assignment to the corresponding group, all individuals will complete a baseline assessment (BA), which includes recording the independent variables and the variables of the primary and secondary results of the study. Then, while the patients are still in hospital, the subjects will be randomly assigned to the control or the experimental group, with the corresponding intervention applied in each of them. Later, two more assessments will be completed, one after 7 days, considered to be the follow-up assessment (FUA), and another at the time of discharge from the hospital, considered to be the final assessment (FA). This can be observed in more detail in Table 1.

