### Data analysis

The statistical analysis will be carried out with the intention to treat. In the descriptive analysis, the population is described by presenting the data as means and standard deviations for the continuous variables and as frequency distributions for the qualitative variables. To evaluate the comparability in the baseline assessment between the two study groups, we will employ the Chi-squared test for qualitative variables and the Student’s T-test for the comparison of the means between the two groups, in addition to the Kolmogorov–Smirnov test to find the normality of the sample. In the inferential analysis, we will consider a confidence interval of 95% (*p* < 0.05), and will use Student’s T-test for related pre and post samples and for independent samples at the end of the study, in addition to a multivariate analysis of variance (MANOVA) with repeated measures (3 levels) to assess interactions between categorical variables, and to determine significant differences between groups and within groups. Additionally, to assess the magnitude of the change in the variables, the effect size of the interventions will be calculated as Cohen’s d (small (0.2), medium (0.5), and large (0.8)) and the partial eta squared (ƞ2p) (small (0.01), medium (0.06), and large (0.14)), where significant, as appropriate with the statistical test applied [25]. We will use Pearson’s Correlation Coefficient to analyse the correlations between the various intervening variables and the parameters established in the different questionnaires and scales employed. A survival follow-up analysis will be completed using the Kaplan–Meier non-parametric method to learn the time of the intervention until the patient’s discharge from hospital, and the survival curves of each of the groups in the study will be compared using the non-parametric logrank test. Processing and analysing the data will be done using the statistics pack SPSS 25.0.

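### Time to hospital discharge is analysed by Kaplan-Meier and log-rank with no provision for in-hospital death; if deaths are censored or excluded, the curves overstate live discharge and the test ignores differences that arise through death

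*Protocol article*

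**What the plan says.** The protocol article, Data analysis, plans a Kaplan-Meier analysis in which the event is hospital discharge and time runs from the intervention. On comparing the arms it states that "the survival curves of each of the groups in the study will be compared using the non-parametric logrank test". On the analysis population it states: "The statistical analysis will be carried out with the intention to treat".

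The withdrawal criteria in the Participants section are "disease progression which brings the patient to a terminal situation or to death, and non-completion of the follow-up and final assessments". Under Evaluations and study plan, the final assessment takes place at discharge. A patient who dies in hospital before discharge therefore meets both withdrawal criteria.

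The Background notes that in some patients with advanced cancer "this dyspnoea may represent a clinical sign of the final phase of the disease". No section says how a patient who dies in hospital enters the discharge curve, and no competing-event method is named. Time to discharge is not among the primary or secondary variables in Description of the variables, and it did not drive the sample size.

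**The concern.** Kaplan-Meier treats a censored patient as someone who will go on to have the event at the same rate as those still under observation. That is reasonable for a patient whose follow-up is cut short. It is not reasonable for one who has died, because discharge has become impossible. Censoring deaths makes the curve describe a hospital in which nobody dies. Excluding deaths makes it describe only patients who lived to be discharged, and it also sits badly with the intention-to-treat statement.

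This is the only time-to-event comparison between arms in the plan, and a finding of earlier discharge would readily be read as benefit. If the arms differ in deaths, by chance or otherwise, the planned curves and test would not show what that does to the chance of leaving hospital alive.

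**Working it through.** **The plan's own figure.** The article gives no figure for time to discharge. Its only sample-size figure concerns the Barthel Index, and it reproduces: 2 × (1.960 + 0.842)² × 8.3² / 7.5² = 19.2, so 20 per arm, and 20 / (1 − 0.20) = 25. It is used below only to set 25 patients per arm.

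**Direction of the error, without assumed rates.** Let the hazards of discharge and in-hospital death be λd and λm. The probability of live discharge by time t accumulates λd × exp(−Λd − Λm), where Λ is the cumulative hazard. The Kaplan-Meier complement with deaths censored accumulates λd × exp(−Λd). The second is never smaller than the first, and it is larger once deaths occur while others remain to be discharged.

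**Size, with assumed constant hazards.** The documents give neither rate, so λd = 0.10 per day is an assumption, and λm = λd × p / (1 − p), where p is the share of stays ending in death.

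- Deaths censored: 1 − KM(t) = 1 − exp(−λd t). At day 30 this is 1 − exp(−3) = 95.0%, whatever p is.
- Live discharge: λd / (λd + λm) × (1 − exp(−(λd + λm) t)).

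| Stays ending in death (assumed) | 1 − KM, day 30 | Discharged alive, day 30 | Excess, points |
|---|---|---|---|
| 5% | 95.0% | 91.0% | 4.1 |
| 10% | 95.0% | 86.8% | 8.2 |
| 20% | 95.0% | 78.1% | 16.9 |
| 30% | 95.0% | 69.0% | 26.0 |

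The excess grows with time: at day 14 it is 2.1 points for 5% and 14.8 points for 30%. With a slower assumed discharge hazard of 1/15 per day, 1 − KM at day 30 is 86.5%, against 80.2%, 73.4% and 66.0% discharged alive for 10%, 20% and 30% death.

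**If deaths are excluded instead.** Time to discharge among the remaining patients follows rate λd + λm. With 20% death that rate is 0.10 + 0.025 = 0.125, and the day-30 reading is 1 − exp(−3.75) = 97.6%, further from 78.1% than under censoring. With 40% death in one arm and 10% in the other, the rates are 0.167 and 0.111 per day, so the arm with more deaths looks faster.

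**The test.** Simulation with 25 per arm, 10,000 runs, a 60-day horizon and two-sided 5%. The log-rank test censors deaths; the Gray-type test keeps patients who die at risk to the horizon. Simulation error is about 0.2 points near 5% and 0.5 points near 45%.

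| Scenario (assumed) | Live discharge by day 60 | Log-rank rejects | Gray-type rejects |
|---|---|---|---|
| No difference | 0.80 vs 0.80 | 5.2% | 5.4% |
| Death hazard only | 0.80 vs 0.89 | 5.5% | 8.9% |
| Death hazard only | 0.70 vs 0.90 | 5.2% | 24.3% |
| Death hazard only | 0.60 vs 0.90 | 5.5% | 45.2% |
| Discharge hazard × 1.5 only | 0.80 vs 0.86 | 24.2% | 16.6% |
| Discharge hazard × 2 only | 0.80 vs 0.89 | 58.2% | 38.7% |
| Discharge × 1.5 and death × 3 | 0.80 vs 0.67 | 22.6% | 7.2% |

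Where the arms differ only through death, the log-rank test rejects at about its nominal level. In the last row it rejects in 22.6% of runs, and the arm with the higher discharge rate is the one that discharges fewer patients alive.

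**The case against.** The strongest objection is that the quoted sentence is compatible with a correct analysis. Keeping patients who die at risk, undischarged, to a fixed horizon is still Kaplan-Meier plus log-rank, and coding rules are often left to a fuller document. This stands in part: the article does not say that deaths are censored or excluded, so the bias is conditional. But the article does make death a withdrawal criterion, and the stated method, applied to withdrawals in the ordinary way, gives the wrong curve. That is more than an omitted detail.

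A reader might infer that the log-rank test is invalid here. The documents do not support that. With deaths censored it is a valid test of the discharge rate among patients still in hospital, it keeps its level, and it has more power than a Gray-type test when only that rate differs (58.2% against 38.7% at a hazard ratio of 2). The added component is training in daily activities and no effect on mortality is hypothesised, so a difference in discharge rate alone is at least as plausible as one in deaths.

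The gain in power is also limited at this sample size. A split of 10% against 30% means 2.5 against 7.5 expected deaths among 25 per arm, and the Gray-type test detects it in only 24.3% of runs. Finally, the Background remark concerns some patients with advanced disease, and entry is not restricted to advanced stage. The plan therefore allows for in-hospital death but gives no basis for its frequency.

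**Conclusion.** The point holds conditionally. If in-hospital deaths are censored or excluded, the planned curves overstate the proportion discharged alive, and the log-rank test cannot see a difference in live discharge that arises through deaths. The direction of the curve error needs no assumed rate. Its size does: 4 to 26 points at day 30 rests on constant hazards, 0.10 discharges per day and 5% to 30% in-hospital death with deaths censored, none of which the documents supply.

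It would go too far to say that the plan certainly produces biased curves, since the handling of deaths is implied rather than stated, or that the trial's main conclusions are at risk. Time to discharge is a supportive analysis, and this point does not affect the Barthel and MRC comparisons.

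**What to change.** In Data analysis, replace the Kaplan-Meier discharge curves with the cumulative incidence of live discharge by arm, with in-hospital death as a competing event, and compare arms by Gray's test. State that all randomised patients are included and no deaths are excluded. Patients withdrawn for terminal progression should be counted by what then happens, discharge or death, because they may still be discharged alive.

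If the work is to stay in SPSS, keep patients who die at risk, undischarged, to a common horizon stated in advance. The horizon has to be named because the study's follow-up otherwise ends at discharge. The recode matches Gray's test when everyone is observed to discharge, death or that horizon.

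Keep the log-rank test, labelled as a cause-specific comparison of discharge rates among patients alive in hospital, and report deaths by arm beside both analyses.

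The cost is slightly more analysis work, software other than the SPSS recode if Gray's test is run directly, and a recorded date of discharge or death for every randomised patient, including those withdrawn; the article does not say whether these dates are kept after withdrawal. Gray's test has less power than log-rank when only the discharge rate differs, which is the reason to retain both. No change to the design or the assessments is needed.

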### Ethical considerations

The study will be carried out thanks to the authorisation of a Clinical Research Ethics Committee of the Area of Health of Salamanca (ID: PI 202007547), having obtained the prior written informed consent of the study subjects and in conformance with the Helsinki Declaration. In it, participants will be informed of the objectives of the project, as well as the risks and benefits of the interventions to be carried out, explained by one of the main investigators. The confidentiality of the subjects included will be guaranteed at all times, in conformance with the laws regarding the protection of personal data and biomedical investigation present in the articles of Spanish Organic Law 3/2018 of 5 December on the protection of personal data and the guarantee of digital rights, and in Regulation (EU) 2016/679 of the European Parliament and of the Council of 27 April 2016 on data protection (GDPR), and within the conditions established by Law 14/2007 on biomedical investigation.

Significant modifications to the protocol (such as changes in the tools of evaluation, modifications to the selection criteria or to the interventions) will be communicated immediately to the Ethics Committee.

And since this is a randomised clinical trial, it follows the CONSORT guidelines, and it was registered. TRIAL REGISTRATION: ClinicalTrials.gov NCT04766593.

### Rigour

This protocol study also follows the evidence-based recommendations of The SPIRIT 2013 Statement for the minimum content of a clinical trial protocol. And the design of the study also follows the evidence-based, minimum set of recommendations of the CONSORT 2010 Statement for conduct parallel-group randomized controlled trials (RCT), enabling readers to understand a trial’s design, conduct, analysis and interpretation, and to assess the validity of its results.

## Discussion

If it is true that there has been an exponential increase in the studies related to the implementation of physical exercise in the intervention of patients with respiratory pathologies, there still remains a problem with the generalisation that those individuals achieve that symptomatic improvement in the completion of their activities of daily living.

The present study will attempt to investigate the influence that rehabilitative measures that are oriented exclusively towards functional recovery and adaptation will have with respect to the measures of physical exercise employed with oncological patients with respiratory symptomatology.

In our daily clinical practice, we have observed first-hand the beneficial effects of physical exercise in the physical improvement of patients with dyspnoea. But we have also observed difficulties with the generalisation of this physical improvement in terms of occupational performance.

Based on the results obtained, we consider it indispensable to establish specific care protocols which improve not only the symptomatology, but also the individual in a more integral manner, which we believe will have positive repercussions on their quality of life and on that of the people around them. Dyspnoea is a symptom that is clearly incapacitating and which increases individuals’ dependence, which is then linked to an exceeding personal cost for their caretakers. By improving patients’ levels of dependence, we are contributing to the reduction of this problem for the caretakers.

### Limitations

The study follows all of the recommendations of CONSORT, but due to the nature of the intervention itself, the participating subjects will not be blinded. However, to minimise any contamination between groups, the investigator responsible for the study measurements at each assessment and the statistical analysis thereof, will be blinded.

### Dissemination plan

The investigator team is planning a rapid and broad diffusion of the results so as to guarantee the maximum visibility of this study. With this aim, the results of the study will be published in open-access, peer-reviewed scientific journals. We will have at least one publication of the primary results, and others planned with the secondary results. This will complement the presentation of the study results at important national and international scientific conferences and seminars. Similarly, we will do a diffusion on social media and other media.

### How potential changes in the study will be approached

Significant modifications to the protocol (such as change in the tools of evaluation, modifications to the selection criteria or to the interventions) will be communicated immediately to the bioethics committee.

## Conclusions

This manuscript presents the protocol of a study aimed at assessing the results of a model of care based on a comprehensive rehabilitation combining a usual multimodal physical exercise programme and a specific programme of recovery of autonomy through activities of daily living training, on functionality, respiratory parameters and quality of life in oncology patients with dyspnea.

## Data Availability

Upon completion of the study, the datasets generated and/or analysed during the current study will be available to those investigators who request it through FAIRsharing of the repositories of research data at https://www.re3data.org/.

## Abbreviations

MRC: Medical research council
SPPB: Short physical performance score
ECOG: Eastern Cooperative Oncology Group
ADL: Activities of daily living
MMSE: Mini-mental state examination
BI: Barthel index
TSK-F: Tampa Scale of Kinesiophobia–Fatigue
WHO: World Health Organization
ACSM: American College of Sports Medicine
EST: Energy-saving techniques
EU: European Union
